#### Objective 4: determining the mechanisms through which NTD exerts its effects

It is hypothesized that the implementation of NTD will lead to improved knowledge, skills, competencies in relation to resident-centredness and collaborative work among team members which in turn should lead to enhanced neighbourhood team practices relative to meeting the residents’ needs (in all domains), resulting in enhanced resident outcomes. A latent growth curve analysis model (combining multi-level modeling and structural equation modeling) will be applied to determine the mechanisms through which NTD exerted change(s) on the outcomes per neighbourhood and for the combined data. As well, a constant comparative analysis of all data will be conducted to uncover any underlying mechanisms that are not explained by the descriptive approaches. Findings from this objective combined with findings from the first three objectives will provide insight in fidelity, contextual factors, effectiveness, and the mechanisms of the effectiveness of NTD on team cohesiveness and resident-centred care in NHs.

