### Aims

The goal of this current study was to implement and evaluate NTD. The specific objectives were to: 1. Examine the fidelity of the program when implemented in a multi-home NH organization; 2. Explore contextual factors associated with implementation and outcomes; 3. Examine the effects of the program on residents, team members, family, and organizational outcomes and the association between the level of implementation fidelity and outcomes, and; 4. Determine the mechanisms through which NTD exerts its effects.

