## Methods

### Design

A multi-component intervention for a single group was used. NTD involved a 30-month implementation plan, starting with a 3-day training for all management and neighbourhood coordinators (NCs), team leaders who are trained to coordinate care service and delivery for two specific neighbourhoods and is the designated primary contact for residents and their family members, followed by individual team development on all neighbourhoods across the home for 12 months. Upon the start of the 2nd implementation year, the second training session for management and NCs took place (3-day training), again followed by a 12-month implementation plan on the neighbourhoods. A third and last training with management and NCs took place at the start of the third implementation year, followed by a 6-month implementation.

Training for management and NCs was delivered by NTD experts over the course of two consecutive days, twice per year, followed a training manual, and included competencies in care coordination, care and service delivery for the neighbourhoods, team’s interpersonal skills and care competencies, care decision support based on group processes, awareness and knowledge to promote residents’ choices, and skills for ongoing supervision and stewardship of the team. Individual team development per neighbourhood was delivered by the NCs on a quarterly base (4 h per session) and consisted of interactive group modules building capacity in team attributes, professional competencies relating to knowledge and skills to support resident centeredness (i.e., resident-centred decision making, reprioritizing care consistent with the residents’ preferences) and competencies in relational care and in the delivery of care and services. The researchers adhered to the Standard Protocol Items: Recommendations for Interventional Trials (SPIRIT) guidelines.

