#### Objective 1: examining the Fidelity of the program

This objective aims at measuring if NTD is delivered as designed. This is addressed by conducting descriptive analyses of the structured observations of staff-resident and team interactions; the surveys and questionnaires; the description of job enactment; and the resident, team members and family satisfaction surveys (Table 2). The quantitative data on fidelity of the program implementation and the observational data will be analyzed descriptively for each site to determine the extent of variation from the planned implementation. In addition, differences in fidelity will be examined across participating sites, using mixed methods. Qualitative data from the semi-structured interviews will be undergoing a constant comparative analysis and will be reviewed separately by two investigators using NVivo 10. Thematic content emerging from the transcripts using an inductive coding technique will be subsequently organized into categorized concepts. The thematic frameworks emerging from the interviews will assist in understanding factors that may contribute to variation in program implementation across the neighbourhoods**.**

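### In a single-group design, the Objective 4 growth model can show that team and resident trajectories are associated, but it cannot determine NTD's mechanism

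*Protocol article*

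**What the plan says.** The Design section of the protocol article states: "A multi-component intervention for a single group was used". Management training is "followed by individual team development on all neighbourhoods across the home for 12 months". It describes no untreated neighbourhoods and no staggered start.

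Objective 4 sets out an ordered hypothesis. NTD improves team knowledge and skills, "which in turn should lead to enhanced neighbourhood team practices relative to meeting the residents’ needs (in all domains), resulting in enhanced resident outcomes". The quantitative tool is named in one sentence: "A latent growth curve analysis model (combining multi-level modeling and structural equation modeling) will be applied", with the purpose to "determine the mechanisms through which NTD exerted change(s) on the outcomes per neighbourhood and for the combined data". That sentence does not say which variable stands for NTD, which measures are mediator and outcome, or how the two are ordered in time.

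Elsewhere the article does hold a graded measure of implementation. Under Objective 1, "differences in fidelity will be examined across participating sites, using mixed methods". The Aims list "the association between the level of implementation fidelity and outcomes" as part of Objective 3. Neither is tied to the Objective 4 model. Table 2 schedules resident scales at baseline and six-monthly. Its staff rows are cut short in the text available, so the timing of the team measures is not known here.

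**The concern.** A mediation claim needs two links: NTD changes team practice, and changed team practice changes resident outcome. With one group, a yes/no NTD term is constant and drops out of the model, on the combined data as well as within a neighbourhood. The first link then reduces to the average time trend in the team measures. Without a stated time order, the second link reduces to an association between team and resident trajectories.

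Two non-causal explanations fit that association equally well. Something that changes to different degrees in different neighbourhoods may move both series. Or residents' condition may drive how staff rate their work and their team. The wording of Objective 4 promises to settle the mechanism, so either explanation could be reported as the way NTD works. The article intends the findings to guide how homes are organised.

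**Working it through.** The article gives no figure for Objective 4, so there is none to reproduce. The check is algebra plus simulation.

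**Units.** The Sample section gives 11 homes of 192 residents, and a neighbourhood has 32: 11 × 192 / 32 = 66 neighbourhoods. The abstract gives 6 homes: 6 × 192 / 32 = 36 if they are the same size. Both are used.

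**Model.** For neighbourhood j at wave t, team practice is M = a + (d + s_M)t + error and resident outcome is Y = c + (d + s_Y)t + error. Here d is drift common to all neighbourhoods, and s_M and s_Y are neighbourhood deviations with SD σ and correlation ρ. Errors have SD τ.

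- First link: the mean slope of M is any NTD effect plus d. With everyone exposed, the two cannot be separated.
- Second link: cov(d + s_M, d + s_Y) = cov(s_M, s_Y) = ρσ². Common drift cancels. Drift that differs between neighbourhoods does not.

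**Slope-on-slope test, two-sided 5%, no team-to-resident path except in the last row.** Setting A: 6 waves, σ = 0.2, τ = 0.5, 1000 runs. Setting B: 7 half-yearly waves, σ = τ = 1, 2000 runs. All are assumptions.

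| Truth | Setting | 66 | 36 |
|---|---|---|---|
| Nothing related | A | 5% | 4% |
| Common drift only, 0.5 slope SD per year | B | 4% | 4% |
| Shared varying cause, ρ = 0.3 | B | 57% | 34% |
| Shared varying cause, ρ = 0.5 | B | 97% | 78% |
| Shared varying cause, ρ = 0.5 | A | 87–88% | 61% |
| Reverse influence, slope correlation 0.3 | B | 58% | 34% |
| Reverse influence, slope correlation 0.5 | B | 95% | 80% |
| Reverse influence, lagged coefficient 0.5 | A | 82–85% | 56% |
| True lagged effect 0.5 | A | 82–83% | 57% |

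In setting A the test fires about equally often for a shared cause, reverse influence and a true effect. In the common-drift row, both mean slopes were nonetheless significant in 94% (66) and 61% (36) of runs with no NTD effect, so the first link fails there.

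**Would a lagged model settle it?** Regress the change in Y from t to t+1 on the change in M up to t, with wave effects and neighbourhood-clustered errors (setting A, 66 neighbourhoods). A true lagged effect of 0.5 is found in about 100% of runs, and reverse influence gives about 7%. Differencing, however, leaves the shared slope in both series. The correlation between the two changes is ρσ² / (σ² + 2τ²). With ρ = 0.5:

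- σ = 0.2, τ = 0.5: 0.02 / 0.54 = 0.04; false path in 7–10%.
- σ = 0.4, τ = 0.5: 0.08 / 0.66 = 0.12; 47%.
- σ = 0.5, τ = 0.5: 0.125 / 0.75 = 0.17; 70%.
- σ = 0.2, τ = 0.1: 0.02 / 0.06 = 0.33; 98%.

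The low rate in the first line reflects noise, not identification. Two further weaknesses:

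- A shared shock (SD 0.3) that reaches teams one wave before residents gives 95% false paths, against 6% for the slope test.
- A true same-wave effect of 0.5 gives covariance 0.5 × (σ² − τ²) = 0.5 × (0.04 − 0.25) = −0.105 between successive changes. The lagged test is then significantly negative in 74–75% of runs.

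**Joint rule.** Claiming a path only if the forward lag holds and the reverse lag does not cuts false claims from 86–99% (slope test) to 1–19% under shared slopes, and from 80% to 0% under reverse influence.

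**The case against.** The strongest reply is that the article does not specify the model closely enough to be faulted. A multilevel structural equation growth model can carry fidelity as a predictor, staffing as a time-varying covariate and lagged paths, and those details may sit in the full protocol or analysis plan. This stands. A reader might infer that the model contains no NTD exposure variable, or that it must relate trajectories over identical waves. The text is silent on the first, and the second cannot be checked without the staff schedule.

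The reply also points out, correctly, that staffing changes and other events are recorded under Objective 2, so they are not unmeasured by design. Objective 4 includes a qualitative analysis and is read with Objectives 1 to 3. The Conclusions leave a controlled study to later work, and the abstract's list of aims omits this objective. These points mean that a false mechanism could be reported, not that it would be.

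The reply does not remove the design limit. An analysis plan cannot create an unexposed group, and a group comparison mentioned under Objective 3 has no second group defined. The fault lies in what is stated: a named model and a promise to determine mechanisms, in a design where that model supports association only.

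**Conclusion.** The point holds in a limited form. As described, the Objective 4 growth model can describe how team and resident trajectories move together, but it cannot determine how NTD works. Change that varies between neighbourhoods, or influence running from residents to team ratings, could be reported as mediation.

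With no true team-to-resident path, the false-path rate for a slope-on-slope test ran from 34% to 99% across the settings tried. It rests on assumed slope correlations, variances, wave counts and 36 or 66 neighbourhoods, and should be quoted only as a range.

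Two stronger readings are tempting and fail. Drift shared equally by all neighbourhoods does not create a slope-on-slope association; it only makes the average trend look like an NTD effect. Nor does the evidence support replacing the growth model with a lagged one, which has its own false paths and can reverse the sign. The matter is worth correcting because the change is cheap. It concerns the last of four objectives.

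**What to change.** 1. State under Objective 4 that growth-curve associations are descriptive, and replace the promise to determine mechanisms with one to explore them.
2. Enter measured fidelity or training dose, by neighbourhood and period where available, as a graded exposure. Use only components that are separate from the team-practice measures: Objective 1 draws fidelity partly from observed team interactions and satisfaction surveys, which overlap with the mediator and outcomes. Sessions delivered would be cleaner.
3. Include the staffing changes and events recorded under Objective 2 as covariates.
4. If the staff waves permit, add forward and reverse lagged paths beside the growth model, within neighbourhood, with wave effects and clustered errors. Claim support for a mechanism only when the forward path holds in the expected direction and the reverse path does not.

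**Cost.** This needs plan wording and additional models on data already collected; the article says analysis is ongoing. One wave is lost to the lag. Same-wave effects are missed or can appear with the wrong sign in a lagged difference model. Confounders that reach teams before residents remain. The joint rule will also withhold a claim where a real effect coexists with a strong shared trend. If staff measures are too sparse for lags, steps 1 to 3 still apply and no mechanism should be claimed from the quantitative data.

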### Ethical considerations

This study received ethics clearance by the Research Ethics Board at the agency (REB-118). Informed consent was obtained from residents, family members and staff. Information letters, group and individual information sessions to explain the study were provided to residents, family members and staff. Investigators and research assistants met with participants individually to obtain written and verbal consent.

## Discussion

This study brings an innovative intervention, NTD, to enhance resident centred care in NHs, consistent with the urgent priorities highlighted in previous research, that is, the redesign of NH services to fit the need and expectations of NH residents and addressing the spectrum of care for older persons with complex needs involving dementia [3, 5]. This study aims to provide evidence that NTD can enhance NH care, including preserving residents’ autonomy and dignity, emphasizing quality of life, promoting best practices, all while working within a framework of accountability by emphasizing team members working to their full scope of practice while providing better coordinated care. This multi-component, mixed method study has the potential to generate high impact results and demonstrate the use of tools and methodologies for NHs and dementia care and research. Furthermore, research goals include a new NH model, better care experiences for residents and families, a solidified approach to seamless team functioning, and a program in which every member is used to its fullest capacity and where the residents come first.

Although NTD could be perceived as an easy potential solution for better quality outcomes in NHs, it is important to realize that a large organizational change, such as the one required for NTD implementation, requires significant organizational commitment and leadership. Financial contributions are required for the physical (re) designs, NTD implementation, and the gathering of the data. The authors’ experience with in-kind and financial support and a strong commitment by the organization’s leadership and teams has led to successful recruitment, implementation and data collection. In addition, this study provides an opportunity to test the data collection measures and procedures, software to extract required data from existing data bases, survey completion sessions, site specific and detailed electronic databases, and electronic data collection logs to keep track of the large amount of data. This information allows the research team to fine tune the outcome measures, the research staffing and allocation, and the budget.

Lastly, the authors observed that previous studies or practices aiming to implement RCC models have been curtailed due to the lack of available funds to cover wage/replacement cost for the participation of NH teams. As for any organizational and care model change, one’s biggest investment ought to be in its team member in order to have quality outcomes. For NTD implementation, all participant compensation costs are covered by the organization, in addition to meeting rooms for the training and neighbourhood team sessions.

## Conclusions

This study is the first in a program of research that will lead to a different way of organizing NHs, innovations in how teams collaborate to best serve the needs of older persons, and important insights on what factors need to be in place for sustainable RCC models. Future research will focus on a multi-site, controlled study to further evaluate the effectiveness of NTD on residents’ well-being. This study is one step forward toward resident centred care delivery in a competent and compassionate manner for people in NHs.

## Data Availability

The data that support the findings of this study are available from the participating LTC homes, but restrictions apply to the availability of these data, which were used under license for the current study, and so are not publicly available. Data are however available from the authors upon reasonable request and with permission of the participating LTC homes.

## Abbreviations

NH: Nursing Homes
NTD: Neighbourhood Team Development
